**Methods and analysis:**

A single-blind, superiority, adaptive randomised controlled trial encompassing a multi-arm multi-stage design will be conducted and reported according to the Standard Protocol Items: Recommendations for Interventional Trials (SPIRIT), Template for the Intervention Description and Replication for telehealth (TIDieR-telehealth), and the Consolidated Standards of Reporting Trials (CONSORT) Extension for Adaptive Designs. Informed consent will be obtained from all participants. Eligible participants will be randomly assigned in a 1:1:1:1:1 ratio to either the control group, receiving education alone, or one of four intervention groups ((1) education, notifications and exercise modules; (2) education, notifications, exercise and sleep modules; (3) education, notifications, exercise and diet modules; and (4) education, notifications, exercise, sleep and diet modules) through the app. The study consists of two stages with the possibility of dropping arms for futility using pre-specified decision rules at the end of the first stage. A total of 370 participants aged 18 years or older, with chronic non-specific LBP, will be recruited Australia-wide from the general community. The primary outcome will be self-reported physical function measured by the Patient-Specific Functional Scale at 6 weeks post-randomisation. Data will be analysed using the Student’s t-test or the non-parametric Mann-Whitney U test.

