### Sample size

The sample size calculation was conducted a priori, considering a MAMS design with five arms (one control arm and four intervention arms) and two stages that consist of one interim and the final analysis. The primary endpoint was established at 6 weeks post-randomisation (ie, immediate post-intervention). A smallest worthwhile effect on the PSFS score (0–30) of 4 points was chosen to estimate the sample size, considering the literature^76^ and the nature of the intervention (ie, a 6-week digital intervention with no face-to-face interaction).

The sample size calculation was based on a two-sided type I error of 5% (significance level), a power of 80% to control for a type II error and an SD of 5.8 using a generalisation of the power requirements for testing multiple active arms to one control group, as proposed by Dunnett.^92^ The calculation resulted in 21 participants per arm at the first stage and 42 participants per arm at the second stage, reaching a total sample size of 315 participants. Allowing for a loss to follow-up rate of 15% at 6 weeks, the study would require a total sample size of 370 participants (n=25 in the first stage and 49 in the second stage per group). This total sample represents the maximum number of participants that will be enrolled when all the intervention arms meet the criteria for being maintained through the second interim stage (ie, no arm is dropped after the interim analysis). Therefore, there is the possibility that the study terminates with a smaller sample size if, at the interim analysis, one or more intervention arms meet the criteria for being dropped. For instance, if one, two or three arms are dropped after the interim, the study sample will decrease to 321, 272 and 223, respectively.

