### Statistical methods

All statistical analyses will be conducted following the intention-to-treat principle. Baseline characteristics will be summarised by arm using descriptive statistics and reported with measures of frequency (proportion), mean, SD and 95% CI. Differences in dichotomous variables will be expressed as risk difference and number needed to treat or number needed to harm with 95% CI. Continuous variables will be summarised and reported with mean and SD in case of a Gaussian (normal) distribution or as the median and IQR in case of a skewed distribution.

At the interim and final analysis, differences in outcome data between each intervention arm and the control group will be analysed using the Student’s t-test in the case of a Gaussian (normal) distribution. Otherwise, the non-parametric Mann-Whitney U test will be used after correcting for baseline differences, if required. Changes in health-related quality of life scores will be analysed using the Wilcoxon test. The Cox proportional hazards regression modelling will be used to adjust for potential confounding factors. For all analyses, statistical significance will be indicated by a p value <0.05.

A planned hypothesis-generating (exploratory) subgroup analysis will be conducted considering diet and sleep. Interaction models will compare the effectiveness of the sleep module in people with low and high scores on the PSQI, as well as the diet module in people with low and high scores on the sQ-HPF. Additionally, a planned exploratory analysis will be conducted to investigate the potential impact of adherence on the magnitude of the treatment effects.

The interim analysis will be conducted after completion of the 6-week intervention programme by the first 25 participants in each arm. Whether and how the trial will continue will be determined by the outcome of the interim analysis, which will allow dropping intervention arms that are deemed futile, in accordance with the following prespecified decision rules considering the primary endpoint (ie, change in mean PSFS score from baseline to 6 weeks after randomisation):

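### The primary PSFS test is chosen after the distribution is seen (t-test or Mann-Whitney), although the endpoint and the planning effect, SD and drop thresholds are in mean PSFS points

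*Protocol article*

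**What the plan says.** Under Statistical methods, the protocol article sets the comparison: "At the interim and final analysis, differences in outcome data between each intervention arm and the control group will be analysed". Student's t-test applies "in the case of a Gaussian (normal) distribution. Otherwise, the non-parametric Mann-Whitney U test will be used", and the sentence ends with a clause on correcting for baseline differences where needed. The Abstract gives the same alternative, "t-test or the non-parametric Mann-Whitney U test", with no criterion for choosing. Continuous variables are summarised by mean and SD, or "as the median and IQR in case of a skewed distribution".

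The same section defines the primary endpoint for the interim rules as "change in mean PSFS score from baseline to 6 weeks after randomisation". Under Sample size, a smallest worthwhile effect "of 4 points was chosen to estimate the sample size", with an SD of 5.8 and a Dunnett-type calculation. The two drop rules are thresholds of 0.5 points against control and 4 points between active arms. The Outcomes section describes the PSFS total as a discrete score from 0 to 30.

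**The concern.** The two branches answer different questions. The t-test concerns a difference in means, which is the quantity the trial was sized for. Mann-Whitney concerns whether a participant in one arm tends to score higher than one in the other. It does not estimate a mean difference, and the protocol names no between-group estimate to go with it. If that branch is taken, the p-value cannot be set against the 4-point threshold.

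The observed data decide the branch. If normality is judged arm by arm or comparison by comparison, some arms may be tested on means and others on ranks. That sits badly with the stated aim of identifying the most effective combination of components. The interim and final analyses could also land on different tests. The trailing clause about correcting for baseline differences adds a second data-driven step, and a plain Mann-Whitney test takes no covariates.

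**Working it through.** **1. Planning basis.** Inputs from Sample size: effect 4, SD 5.8, two-sided 5%, power 80%, four comparisons with one control. The simulated two-sided Dunnett critical value (correlation 0.5) is 2.441. Requiring 80% power to detect 4 points in all four comparisons gives n = 63.7 per arm. The stated figure is 21 + 42 = 63 per arm, or 315 in total. At n = 63 the all-comparisons power is 79.3%. This ignores the interim drop rules. The stated size is therefore reproduced, within rounding, as a comparison of means.

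**2. What each test measures.** For normal data, a 4-point shift on the Mann-Whitney scale is P(X>Y) = Φ(4/(5.8 × √2)) = Φ(0.488) = 0.69. That probability cannot be set directly against 4 points. The hypotheses can also diverge: with equal means, equal SDs and opposite skewness (+1/-1), Mann-Whitney rejects in 15.5% of simulated trials and the t-test in 5.1%. This is a deliberately extreme contrast.

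**3. How often the tests would be mixed.** The document names no check, so these are assumptions: Shapiro-Wilk at 5% in each arm; Mann-Whitney for a comparison if either arm fails; 63 per arm; PSFS as three rounded 0-10 items; baseline mean 12; latent baseline/follow-up correlation 0.5. The baseline follows from the protocol's statement that a 45% improvement corresponds to 5.4 points: 5.4/0.45 = 12. Adding its 30% natural recovery gives a control mean at 6 weeks of 12 × 1.30 = 15.6. Control means of 18 and 21 were also run, each with effects of 0, 2.5 and 4 points.

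- Change scores, all nine settings: 18-26% of trials use different tests for different arms, and 5-8% use Mann-Whitney for all four. The shares hardly depend on the effect or the control mean.
- Raw 6-week scores: about half of trials are mixed at control mean 15.6 with a 4-point effect. At control mean 21 with a 4-point effect, 95-98% put all four comparisons on Mann-Whitney, because scores approach the ceiling.

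**4. Error rates and power.**

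- When arms share a shape, type I error per comparison under the switching rule is 4.9-5.3%.
- At a 2.5-point effect the t-test and Mann-Whitney verdicts differ in about 6-8% of comparisons.
- At 4 points, n = 63 and unadjusted 0.05, t-test power is Φ(4/5.8 × √(63/2) - 1.96) = Φ(1.91) = 97%. Simulated t-test power is also about 97% for normal data and for skewness 0.5 and 1. Mann-Whitney gives 96-98%.

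**The case against.** The strongest reply is that the practical harm is small and partly inferred. Several parts of it stand.

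- **Unit of the check.** The text says which groups are compared, not whether normality is judged per arm, per comparison or once overall. One pooled check would give all arms the same test at a given analysis. The mixed-test figures are therefore conditional. The change of estimand remains.
- **Which variable.** A reader might infer that an effective arm drifts to the ceiling, is the arm most likely to be called non-normal, and that most trials would end up mixed. That holds only for raw 6-week scores. The Abstract and Outcomes sections allow that reading, but Statistical methods names the change from baseline, where the link to the effective arm disappears.
- **Comparing arms.** A reader might infer that arms could no longer be compared. The drop rules are worded on mean change and stay in points whichever test is used.
- **Error control.** A reader might infer inflated type I error. The calculations do not show it when arms share a shape.
- **No answer in points.** Medians are in PSFS points, and so is a Hodges-Lehmann shift. The unseen analysis plan could name an estimate. Neither is the mean difference used for planning.

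An unseen plan could also supply a normality criterion, but the choice would still depend on the data. That rule is stated in the protocol itself, so this is not a detail merely left out.

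**Conclusion.** The point holds as one about estimand and interpretability. The protocol plans, sizes and adapts the trial on mean PSFS points, then lets the observed distribution decide whether the primary test addresses a mean at all. On the Mann-Whitney branch its p-value cannot answer whether 4 points was reached.

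Under the assumed per-arm check, roughly one trial in five to one in four would mix tests on change scores, and 5-8% would use ranks throughout. The shares are much higher for raw scores near the ceiling, and mixing vanishes with one pooled check. The figures rest on the assumed normality test, item structure, baseline mean and correlation. Neither type I error nor power gives a reason to keep the switch.

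**What to change.** Delete the distribution-dependent choice for PSFS in Statistical methods and in the Abstract. For every intervention arm, whatever the observed shape, pre-specify the mean difference from control using a linear model with heteroscedasticity-robust standard errors. Report it in PSFS points with its CI against the 4-point threshold. Keep Mann-Whitney only as a named sensitivity analysis.

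The cost is two sentences and no new data. The sample size basis is unchanged because it is already a comparison of means. Power is essentially unaffected: in the skewness-1 runs the t-test had about 97% and Mann-Whitney about 98%.

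### The primary test is chosen by the observed distribution and baseline is corrected for only conditionally, so the final effect measure is not fixed and precision is given away

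*Protocol article*

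**What the plan says.** Under Statistical methods, the protocol article sets one scheme for the interim and final comparison of each intervention arm with control. Student's t-test is used when the distribution is Gaussian; if not, "the non-parametric Mann-Whitney U test will be used after correcting for baseline differences, if required". The abstract repeats the either/or choice. The section then names Cox proportional hazards regression for adjusting for confounders. No other adjustment model appears for the comparison of arms.

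The interim rules that follow define the primary endpoint as "change in mean PSFS score from baseline to 6 weeks after randomisation", with thresholds of 0.5 and 4 points.

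Under Sample size: "A smallest worthwhile effect on the PSFS score (0–30) of 4 points was chosen to estimate the sample size". The calculation uses a two-sided 5% error, "a power of 80% to control for a type II error and an SD of 5.8", and a method for "testing multiple active arms to one control group, as proposed by Dunnett". It arrives at 21 + 42 = 63 evaluable participants per arm, 315 in total, and 370 after 15% loss. The article does not say whether 5.8 is the SD of the week-6 score or of the change.

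Under Primary outcome and in Table 1, the PSFS is a 0–30 sum score, recorded at baseline and again at 6, 12 and 52 weeks.

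**The concern.** Three things are left to the data or to later judgement.

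- **Effect measure.** A t-test goes with a difference in means; Mann-Whitney compares ranks. The branch is picked by the observed distribution, so it can differ among the four comparisons. The trial is sized to detect 4 mean points, yet the final analysis may not report a mean difference.
- **Baseline adjustment.** It is conditional, without a stated trigger or method. As the sentence is built, it belongs to the Mann-Whitney branch, and that test takes no covariate. The one regression model named is for time-to-event data.
- **Precision.** Every participant gives a baseline PSFS. A week-6 t-test ignores it. A change-score t-test uses it with a fixed weight of one, which is not the efficient weight. The lost precision affects the final estimates and also the interim, where arms are dropped on point differences from few participants.

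**Working it through.** **Inputs.** From Sample size: two-sided alpha 0.05, power 80%, difference 4, SD 5.8, Dunnett comparison of four arms with one control, 63 evaluable per arm. From Statistical methods: interim after 25 per arm complete the programme (21 evaluable after 15% loss, per Sample size). Assumed, because the article gives no figure: baseline to week-6 correlation ρ of 0.3, 0.5 and 0.7, and equal SD s at both visits.

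**1. The plan's own figure.** The two-sided Dunnett critical value for four comparisons sharing a control (correlation 0.5) is 2.442. Requiring 80% power to reject all four at difference 4 and SD 5.8 gives 64 per arm (320), against the stated 63 (315). Power at 63 is 79%. The figure is reproduced within rounding. The article does not define power; the all-four reading is inferred from the match, since power for one given comparison needs 46 per arm and power for any comparison 26. No baseline correlation enters the calculation.

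**2. Precision.** Variance per participant:

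- week-6 score: s²
- change score: 2(1 − ρ)s²
- baseline-adjusted (ANCOVA): (1 − ρ²)s²

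The ratio of adjusted to change-score variance is (1 − ρ²) / [2(1 − ρ)] = (1 + ρ)/2. The ratio of adjusted to week-6 variance is 1 − ρ².

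| ρ | adjusted ÷ change | adjusted ÷ week 6 | n per arm, all-four 80%, if 5.8 is SD of change | the same, if 5.8 is week-6 SD |
|---|---|---|---|---|
| 0.3 | 0.65 | 0.91 | 42 | 58 |
| 0.5 | 0.75 | 0.75 | 48 | 48 |
| 0.7 | 0.85 | 0.51 | 55 | 33 |

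The comparator is 64 per arm without adjustment. With 63 per arm kept, all-four power rises from 79% to 97%, 93% and 88% (5.8 as SD of change) or to 85%, 93% and 99.5% (5.8 as week-6 SD).

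**3. Interim standard error, taking 5.8 as the SD of change.** SE = 5.8 × √(2/n).

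- n = 21: 5.8 × √(2/21) = 1.79. Multiplying by √0.65, √0.75 and √0.85 gives 1.44, 1.55 and 1.65.
- n = 25: 5.8 × √(2/25) = 1.64, falling to 1.32, 1.42 and 1.51.

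As an illustration, take four equally effective arms with 21 evaluable each. The chance that the best and worst differ by more than 4 points, so that an arm is dropped by chance under the second rule, is the tail of the range of four independent means at 4 / (5.8/√21) = 3.16 standard errors, about 11%. With adjustment at ρ = 0.5 it is about 5%.

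**4. Type I error per comparison (simulated, 63 per arm, nominal 0.05).**

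- Mechanical choice of test by a normality check (Shapiro-Wilk at 0.05, assumed): 0.048 to 0.051. Mann-Whitney is chosen in about 10% of normal samples, 30% of mildly bounded samples and over 99% of skewed or ceiling-bound samples.
- Free choice of the smaller p value from t-test and Mann-Whitney: 0.055 to 0.067.
- Adjusting only when a baseline test gives p < 0.05, against an unadjusted week-6 t-test: 0.043 (ρ = 0.5) and 0.037 (ρ = 0.7).
- Free choice between unadjusted and adjusted results: 0.074 (ρ = 0.5) and 0.083 (ρ = 0.7).

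**The case against.** **The plan is valid and was sized without adjustment.** An unadjusted comparison in a randomised trial is unbiased, and the stated sample size can be reproduced without any correlation. This stands: the precision point is a gain forgone, not an error. Its size depends on ρ and on which SD 5.8 is, and the two readings move in opposite directions with ρ.

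**A test picked by the data does little harm to type I error.** This also stands for a mechanical rule. The risk lies in discretion, and a correction whose trigger is not stated leaves discretion. The SAP may define a trigger. Even so, the protocol would still have adjustment depend on the data and the final effect measure undecided between means and ranks.

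**A reader might infer that Mann-Whitney defeats the interim thresholds.** It does not. The drop rules are written on mean PSFS change, which can be computed whichever test is run, and no early stopping for efficacy is planned. The open effect measure matters at the final analysis.

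**A reader might infer that participants without a week-6 score are left out.** The named tests do need a week-6 value, and the sample size has "Allowing for a loss to follow-up rate of 15% at 6 weeks". But the article also says "All statistical analyses will be conducted following the intention-to-treat principle" and never says such participants are excluded. Either test could be run on imputed data. The only sentence ruling out imputation, under Data collection methods, concerns participants who ask for all their data to be withdrawn. Handling of missing values is commonly left to the SAP, so this is no finding.

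**Conclusion.** The point holds as a matter of stated text: the choice of test depends on the observed data, baseline correction is conditional and undefined, and the one adjustment model named does not suit the outcome. There are three consequences.

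- The final effect measure is not fixed, although the sizing is in mean points. This needs no assumption.
- Discretion over adjustment could take type I error per comparison from 0.05 to about 0.07 to 0.08. This is the result of a fully free choice at ρ 0.5 to 0.7, not a prediction of what the team will do.
- Precision is lost: 15% to 35% of the variance against a change-score t-test, or 9% to 49% against a week-6 t-test, for assumed ρ of 0.3 to 0.7. At ρ = 0.5 both are 25%.

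The change is worth making because it has no real downside, not because the present plan is invalid.

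**What to change.** Name one primary analysis: a linear model (ANCOVA) for week-6 PSFS, or a mixed model for PSFS at 6, 12 and 52 weeks. Always adjust it for baseline PSFS, and report the week-6 mean difference of each arm against control with its confidence interval. Remove the distribution-dependent choice of test and the conditional correction, and keep the rank test as a sensitivity analysis. Delete Cox regression as the adjustment model for the PSFS; any further prespecified covariates go into the same linear model. Apply the existing interim rules, thresholds unchanged, to the ANCOVA-adjusted mean difference. Say whether 5.8 is the SD of change or of the week-6 score. Record the change before anyone sees outcome data by arm; if the interim has already been run, confine it to the final analysis and document this.

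The cost is protocol and SAP wording and a little programming. No new data and no larger sample are needed.

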### Objectives

The purpose of this study will be to determine, through an adaptive MAMS RCT, whether the My Back Exercise app, consisting of a 6-week, automated, tailored exercise intervention, standard LBP education, educational push notifications, a sleep educational programme and diet advice, compared with a control intervention, consisting of app-based standard LBP education, is effective for improving physical function in people with chronic non-specific LBP at 6 weeks after randomisation (ie, immediate post-intervention). In addition, this study aims to identify which combination of components within the My Back Exercise app is the most effective for eliciting improvement in physical function. The secondary aim of this study will be to determine whether the My Back Exercise app is effective for improving secondary outcomes when compared with app-based standard LBP education for people with chronic non-specific LBP. Secondary outcomes will include pain intensity, pain frequency, disability, health-related quality of life, sleep quality, consumption of highly processed food, exercise importance, exercise self-efficacy, adherence to exercise recommendations, co-intervention use, health literacy level, global perceived effect, impression of change, overall satisfaction, usefulness of the app and frequency of the push notifications. Additionally, data will be collected on process measures (ie, conversion rate, recruitment rate and rate of completed follow-up), the smallest worthwhile effect and adverse events.

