#### Secondary outcomes

Secondary outcome measures will be grouped into domains and will include:

Symptoms and function:

Pain intensity, measured by the Numeric Rating Scale (NRS)^78^ at baseline, 6, 12 and 52 weeks after randomisation.Pain frequency, measured by a self-reported question at baseline, 6, 12 and 52 weeks after randomisation.Disability, measured by the Roland-Morris Disability Questionnaire (RMDQ)^56 79^ at baseline, 6, 12 and 52 weeks after randomisation.

Quality of life and general health:

Health-related quality of life (HRQoL), measured by the EuroQol 5-Dimension 5-Level (EQ-5D-5L)^80^ at baseline, 6, 12 and 52 weeks after randomisation.Sleep quality, measured by the Pittsburgh Sleep Quality Index (PSQI)^81 82^ at baseline, 6, 12 and 52 weeks after randomisation.Consumption of highly processed food, measured by the Short Screening Questionnaire of Highly Processed Food Consumption (sQ-HPF)^64^ at baseline, 6, 12 and 52 weeks after randomisation.

Health behaviours and beliefs:

Exercise importance, measured by a self-reported question at baseline and 6 weeks after randomisation. Participants indicate how important it is to them to do regular exercise to manage their back condition. Answer options are presented on a 7-point Likert-type scale ranging from 1=‘not at all important’ to 7=‘extremely important’, where higher scores indicate higher importance.Exercise self-efficacy, measured by the Self-Efficacy for Exercise (SEE) Scale^83^ at baseline, 6, 12 and 52 weeks after randomisation.Adherence to exercise recommendations, measured by the Exercise Adherence Rating Scale (EARS)^84^ at 6 weeks after randomisation.

Healthcare utilisation and engagement:

Co-intervention use, measured by a self-reported questionnaire specifically designed for this study at baseline, 6, 12 and 52 weeks after randomisation.Health literacy level, measured by the Health Literacy Questionnaire (HLQ)^85^ at baseline, 6, 12 and 52 weeks after randomisation.

Patient perception of change:

Global perceived effect, measured by the Global Perceived Effect (GPE) scale^86^ at 6, 12 and 52 weeks after randomisation.Impression of change in overall status, measured by the Patient’s Global Impression of Change (PGIC)^87^ at 6, 12 and 52 weeks after randomisation.

Satisfaction and usability of the app:

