If the change in an intervention arm is no more than 0.5 points greater than the control group, this intervention arm will be dropped. Under this rule, all four intervention arms may be dropped, and the trial terminated. This decision rule was established based on previous adaptive trials investigating conservative interventions in the field of musculoskeletal health.^96^If the change in one intervention arm is more than 4 points higher than the other, the worst-performing intervention arm will be dropped. This decision rule was established considering the smallest worthwhile effect on disability, reported in previous studies as a 15% incremental improvement beyond the natural recovery.^97^ Natural recovery, in turn, is considered a 30% improvement from baseline. Based on our previous study (EMPoweR), a 45% improvement from baseline would correspond to a 5.4-point between-group difference. For this study, this effect size was downgraded to 4 points due to the nature and duration of the intervention (ie, a 6-week digital intervention with no face-to-face interaction).

The decision rules were carefully designed to minimise the risk of prematurely and incorrectly dropping promising treatment arms, potentially leading to a failure to reject the null hypothesis (type II error), while ensuring that the preplanned adaptations would still guarantee increased trial efficiency. Two complementary decision rules were proposed to account for the comparison between each treatment arm against the control group (first rule) and the pairwise comparison among all treatment arms (second rule). Both decision rules are intended to work as indicators of futility, therefore configuring a ‘drop-the-loser’ design that also allows early stopping for futility. Early stopping for efficacy was not planned in this trial.

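### The quality-of-life analysis names an unspecified Wilcoxon test; the more natural reading is a within-arm test, which would not answer the comparative secondary aim

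*Protocol article*

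**What the plan says.** All of the analysis text is in the Statistical methods section of the protocol article.

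- The general rule for outcomes is that "differences in outcome data between each intervention arm and the control group will be analysed using the Student’s t-test" when the data are Gaussian. If they are not, "the non-parametric Mann-Whitney U test will be used after correcting for baseline differences, if required".
- Quality of life then gets its own sentence: "Changes in health-related quality of life scores will be analysed using the Wilcoxon test". No arms, comparator or pairing are named.
- The threshold is common to everything: "For all analyses, statistical significance will be indicated by a p value <0.05".

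The Objectives section lists health-related quality of life among the secondary outcomes. It frames the secondary aim as whether the app is "effective for improving secondary outcomes when compared with app-based standard LBP education". Under Secondary outcomes, quality of life is the EQ-5D-5L, collected at baseline and at 6, 12 and 52 weeks.

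**The concern.** Two rank tests share the Wilcoxon name. The rank-sum test is the Mann-Whitney U test and compares two independent groups. The signed-rank test is for paired data and asks whether one group changed.

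The section has just named the first of these as Mann-Whitney U. A differently named test, applied to changes in one outcome, therefore points towards the signed-rank test. If the rank-sum test were intended, the sentence would add nothing to the general rule.

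A signed-rank test within an arm asks whether that arm improved over time. The stated aim asks whether it improved more than control. People who enrol with chronic pain may improve in every arm, and the article itself allows for this: "Natural recovery, in turn, is considered a 30% improvement from baseline". An analyst who followed the signed-rank reading could report significant quality-of-life gains in several intervention arms that carry no information about the app against education alone.

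**Working it through.** **The plan's own figures.** The article gives no expected change, SD or power for EQ-5D-5L. The only relevant figure is the arm size in the Sample size section: 21 + 42 = 63 evaluable per arm, and 5 × 63 = 315. This reproduces: with a 4-point effect, SD 5.8, a two-sided Dunnett critical value of 2.44 and no interim look, 63 per arm gives 79.4% power to reject all four null hypotheses, close to the stated 80%. It is used below only as the arm size.

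**Reading A: signed-rank within an arm.**

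Inputs: n = 63 per arm and a 5% two-sided level (article); normal change scores with the same mean d, in SD units of the change score, in every arm (assumption). The true between-arm difference is zero. Results from 4,000 simulated runs per setting:

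| Common improvement d | Signed-rank in one intervention arm, p < 0.05 | Mann-Whitney U against control, p < 0.05 |
|---|---|---|
| 0 | 4.6% | 4.6% |
| 0.3 | 63% | 5.0% |
| 0.5 | 97% | 5.2% |

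A further 1,500 simulated trials at d = 0.2 gave 33% for signed-rank.

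A rough hand check uses the paired z-test, which is slightly more powerful than signed-rank under normality:

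- d = 0.3: 0.3 × √63 = 2.38; 2.38 − 1.96 = 0.42; Φ(0.42) ≈ 0.66.
- d = 0.5: 0.5 × √63 = 3.97; 3.97 − 1.96 = 2.01; Φ(2.01) ≈ 0.98.

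Both lie just above the simulated values, as expected. Within-arm tests in different arms share no data. With four intervention arms retained, the chance of at least one significant arm at d = 0.3 is therefore 1 − (1 − 0.63)^4 = 1 − 0.37^4 ≈ 0.98.

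**Reading B: rank-sum on change scores.**

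This compares arms and keeps its 5% level, as the last column shows. What is lost is efficiency and an effect estimate. Assume equal variance σ² at baseline and follow-up, with correlation r:

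- variance of a change score: 2σ²(1 − r)
- residual variance after regression on baseline: σ²(1 − r²)
- ratio: (1 − r²) / [2(1 − r)] = (1 + r)/2

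| Assumed r | Variance ratio | Per-arm size at which change scores match 63 adjusted |
|---|---|---|
| 0.3 | 0.65 | 63/0.65 ≈ 97 |
| 0.5 | 0.75 | 63/0.75 = 84 |
| 0.7 | 0.85 | 63/0.85 ≈ 74 |

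The ratio is exact for mean-based analyses of change and only approximate for a rank test on changes. The article gives no r for EQ-5D-5L.

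**Adjustment available in the text.** Correction for baseline is attached to Mann-Whitney U, if required, and not to the Wilcoxon sentence. The only adjustment model named is Cox regression, which does not fit a questionnaire score.

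**The case against.** The strongest reply is that the text never says signed-rank, paired or within-arm. The general rule covers outcome data for each intervention arm against control and does not exclude quality of life, so the Wilcoxon sentence could be an addition to that comparison. Nor does the word changes settle the matter: the same section defines the primary endpoint as a change from baseline, and its futility rules compare that change between arms. All of this stands. A reader might infer that the plan prescribes a within-arm test and leaves every intervention arm uncompared with control on quality of life. The article does not establish that; it leaves it open.

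Three further points stand in part.

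- The 30% natural-recovery figure is given to justify a decision rule and concerns disability. It makes a general improvement plausible, but gives no size for EQ-5D-5L. The 0.3 and 0.5 SD inputs are assumptions.
- A reader might say that a rank-sum test would ignore baseline. It would not, because a change score subtracts baseline. It only uses baseline less efficiently than a covariate does.
- An unpublished SAP may clarify the test. But the article makes a positive choice of test for a named outcome, and that choice is unclear as printed.

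The reply does not rescue the sentence. On one reading it fails to serve the stated aim; on the other it is redundant and weaker than an adjusted comparison.

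**Conclusion.** The point holds as an ambiguity with a harmful natural reading, not as proof that control comparisons are absent. The article does not say which Wilcoxon test or which contrast applies to quality of life.

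If signed-rank is meant and used alone, about 63% to 97% of arms would show significance with no treatment effect. This assumes a common improvement of 0.3 to 0.5 SD, normal change scores and 63 evaluable per arm. If no improvement occurs, the rate is about 5%. If rank-sum is meant, the error rate is sound, and the cost is a duplicated test, no adjusted effect estimate, and an efficiency loss set by a variance ratio of 0.65 to 0.85 for assumed r between 0.3 and 0.7.

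One secondary outcome is affected, and the sentence should be corrected before the final analysis.

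**What to change.** Replace the Wilcoxon sentence. State that EQ-5D-5L at 6, 12 and 52 weeks will be compared between each intervention arm and control, adjusted for baseline EQ-5D-5L by ANCOVA or a mixed model for the repeated follow-ups, and reported as the adjusted between-arm difference with 95% CI. State also that within-arm change is descriptive only, without p values. If skewness prompted the rank test, robust or bootstrap standard errors deal with it and keep the effect estimate.

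The cost is one or two sentences in an amendment, and the same wording in the SAP. No new data are needed, because EQ-5D-5L is already collected at baseline and at all three follow-ups. The change should be made by people who have not seen quality-of-life results by arm.
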